**Figure 1 F1:**
[figure not shown]
**Food C**hallenge at **HO**me or in **M**edical **P**ractice (FoodCHOMP) participant flow. Food Allergy Quality of Life (QoL) is assessed at 1 & 6 months.

Participants will be advised to cease the challenge immediately if symptoms occur and to follow their prescribed standardised Australian Society for Clinical Immunology & Allergy (ASCIA) Action Plan for Allergic Reactions or Anaphylaxis. Contact details for the research team will be provided for reporting adverse events (AEs).

Participants will be eligible to have one food allergy label assessed through this trial. Where an individual has multiple eligible food allergy labels, the selection of the food allergen to be investigated within this trial will be at the discretion of the participant. Further food allergy labels that remain at the end of the trial will be assessed as per standard of care.

#### In-clinic food challenge (Control arm)

Participants randomised to the control arm will undergo a standard in-clinic OFC, following existing protocols at participating sites. Challenges are performed using a four-step protocol adapted from the PRACTALL^5^ guidelines, with incremental doses administered at regular intervals over several hours under direct medical supervision.^5^ The dosing schedule for the in-clinic challenge is presented in figure 1 and doses are drawn from the Food Allergy Challenge Doses table (online supplemental material 1). Participants will be observed for at least 2 hours after the final dose to monitor for delayed reactions.

In both study arms, participants will be provided with an ASCIA Action Plan if clinically indicated and, where appropriate, prescribed an epinephrine device for use in the event of severe reactions.

### Outcomes

The primary outcome is the safety of home-based OFC, measured by the proportion of participants who experience an immune-mediated AE during the food challenge. Immune-mediated AEs are defined as symptoms indicative of an IgE-mediated hypersensitivity reaction to the challenge food, as defined by the PRACTALL guidelines.^9^ AEs will be reviewed to determine the severity and causality (immune-mediated vs non-immune-mediated) by an independent panel consisting of two allergy specialists from non-participating sites. In the event of discordant assessment between the two allergists, the decision will be passed onto a third clinician.

In addition to the primary safety outcome, the study will assess a range of secondary outcomes evaluating recruitment feasibility, protocol adherence and the occurrence of non-immune mediated AEs (Box 2). These measures will help determine whether home-based challenges are practical and acceptable in routine clinical practice. Furthermore, exploratory outcomes will investigate patient-reported quality of life, rates of sustained food reintroduction and potential health economic impacts, providing insights into the broader clinical and societal implications of adopting home food challenges.

Box 2Secondary and exploratory outcomes
*Secondary outcomes*
Secondary outcomes include:Proportion of participants who experience non-immune-mediated adverse events during the food challenge, including:Taste aversionAnxiety preventing completion of the challenge.Feasibility outcome measures:Eligibility to screened ratio (*proportion of screened patients who meet eligibility criteria*).Recruitment to eligibility ratio (*proportion of eligible patients willing to participate*).Intervention to recruitment ratio (*proportion of recruited patients who complete oral food challenge*).Identification of barriers to protocol completion in the home challenge arm, assessed through participant interviews.Protocol compliance in both study arms.Utility outcome:Proportion of participants identified as tolerant to the implicated food after challenge.
*Exploratory outcomes*
Exploratory outcomes include:Change in food allergy-related quality of life, assessed using the Food Allergy Quality of Life Questionnaire-12 at baseline, 1 month and 6 months postchallenge (online supplemental material 3).Degree of active consumption of the implicated food following a negative challenge result 1 month and 6 months postchallenge.Time from referral to completion of food challenge.Health economic impact of home-based compared with in-clinic food challenges.

Participants in both arms will undergo baseline, 1-month and 6-month food allergy quality of life assessment using the FAQLQ-12 and assessment of degree of consumption of the challenged food (online supplemental material 3).^14^

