### Sample size and statistical analysis

A total of 120 participants (60 per arm) will be recruited for this pilot trial. This sample size will provide estimates of safety and recruitment feasibility outcomes with a precision of <20% (total width of CIs). The chosen sample size is also considered sufficient to generate reliable estimates of safety and potential efficacy for planning a future definitive trial, as precision gains diminish beyond approximately 60 participants per group for binary outcomes.^15^

All analyses will follow the intention-to-treat principle, with supplementary per-protocol analyses conducted for sensitivity. Continuous variables will be summarised as medians with IQRs, while categorical variables will be presented as frequencies and percentages.

Binary outcomes will be presented as counts and proportions with exact 95% CIs. Comparative analyses between study arms will report absolute risk differences and relative risks, each with 95% CIs, using generalised linear models with a binomial family and identity or log link functions as appropriate.

No interim analyses are planned for this pilot study. Missing data are expected to be minimal and, where necessary, will be described in reporting.

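### The exploratory consumption outcome is defined only after a negative challenge, so comparing arms on it conflicts with the stated intention-to-treat rule and is open to selection bias

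*Protocol article*

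**What the plan says.** Three statements in the protocol article bear on this point.

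- **Outcome definition** (Outcomes, Box 2, exploratory outcomes): "Degree of active consumption of the implicated food following a negative challenge result 1 month and 6 months postchallenge".
- **Data collection** (the paragraph after Box 2): participants in both arms have, at baseline, 1 month and 6 months, a quality-of-life questionnaire and "assessment of degree of consumption of the challenged food". Nothing here limits the assessment to those with a negative challenge.
- **Analysis principle** (Sample size and statistical analysis): "All analyses will follow the intention-to-treat principle, with supplementary per-protocol analyses conducted for sensitivity". No class of outcome is exempted.

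Box 2 also lists "Time from referral to completion of food challenge" as an exploratory outcome. It is discussed under the objection only.

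**The concern.** Whether a participant has a negative challenge is known only after allocation, and the allocated setting can influence it. According to Treatment arms, the home challenge needs daily dosing over 5 days after a supervised first dose, while the clinic challenge is completed over several hours under supervision. The secondary outcomes include anxiety that prevents completion, and interviews about barriers to completion in the home arm. The Introduction attributes failure to reintroduce a tolerated food to anxiety or lack of confidence. The same trait can therefore remove a participant from the denominator and also make that participant less likely to eat the food.

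If so, the participants left in the arm with fewer negative results are a more confident group, and the conditional rate flatters that arm.

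What is at stake is planning. The Introduction names better real-world reintroduction as a possible benefit of home challenge, and the sample-size section says the pilot should give estimates of potential efficacy for a definitive trial. A point estimate with the wrong sign would be a poor input to that.

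**Working it through.** **The plan's own figure.** The sample-size section claims estimates "with a precision of <20% (total width of CIs"). With exact (Clopper-Pearson) intervals, the widest case at n = 120 is 60/120, with width 18.5%, so the claim holds for the whole sample. At n = 60 it holds up to 9/60 (width 19.5%) and, by symmetry, from 85% upwards; at 30/60 the width is 26.4%. The figure reproduces for the total sample and for low or high per-arm rates. The present point does not depend on it.

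**Inputs**
- 60 randomised per arm (Sample size and statistical analysis).
- Reintroduction after a tolerated in-clinic challenge: the Introduction cites 20%–40% failing to reintroduce, so 60%–80% do.
- Share with a negative challenge in each arm: not given, so every value below is an assumption.

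**Formula.** Let q be the share of an arm with a negative challenge and r the consumption rate among those participants. The outcome as defined compares r_home with r_clinic. Over all randomised, the rate is q × r. Home looks better among negatives but worse among all randomised when

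r_clinic < r_home < (q_clinic / q_home) × r_clinic.

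If q_clinic = q_home, this interval is empty and no reversal is possible.

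**Illustration (assumed counts).** Home: 45 of 60 negative, 36 eating the food. Clinic: 57 of 60 negative, 40 eating the food.

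| Denominator | Home | Clinic | Difference | 95% CI |
|---|---|---|---|---|
| Negatives only | 36/45 = 80.0% | 40/57 = 70.2% | +9.8 points | -7.4 to +25.6 |
| All randomised | 36/60 = 60.0% | 40/60 = 66.7% | -6.7 points | -23.2 to +10.4 |

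Check against the condition: the upper limit is (57/60)/(45/60) × 40/57 = 40/45 = 88.9%, and 80.0% lies between 70.2% and 88.9%.

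The intervals are Newcombe's, built from Wilson limits (l, u) for each arm: lower = d − √[(p₁ − l₁)² + (u₂ − p₂)²], upper = d + √[(u₁ − p₁)² + (p₂ − l₂)²].
- Negatives only: Wilson limits are 0.662–0.891 (home) and 0.573–0.805 (clinic). Lower = 0.098 − 0.172 = -0.074; upper = 0.098 + 0.157 = 0.256 (from unrounded values).
- All randomised: Wilson limits are 0.474–0.714 and 0.541–0.773. Lower = -0.067 − 0.165 = -0.232; upper = -0.067 + 0.170 = 0.104 (from unrounded values).

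**Other assumed counts.** Home 43/60 negative with 34 eating, clinic 54/60 negative with 38 eating: 34/43 − 38/54 = 79.1% − 70.4% = +8.7 points (CI -9.0 to +25.0). Over all randomised, 34/60 − 38/60 = -6.7 points (CI -23.4 to +10.6).

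**How wide the window is.** Take q_clinic = 0.90:

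| r_clinic | q_home | r_home values that reverse the sign |
|---|---|---|
| 0.70 | 0.90 | none |
| 0.70 | 0.85 | 0.70 to 0.74 |
| 0.70 | 0.80 | 0.70 to 0.79 |
| 0.70 | 0.75 | 0.70 to 0.84 |
| 0.60 | 0.80 | 0.60 to 0.675 |
| 0.80 | 0.80 | 0.80 to 0.90 |

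A 5-point gap in negative results leaves a narrow window; a gap of 10 to 15 points leaves a substantial one.

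**The case against.** **The conditional rate answers a real question.** The gap described in the Introduction is failure to reintroduce a food that was tolerated, and that has meaning only after a tolerated challenge. A participant with a positive challenge who avoids the food is not a reintroduction failure. This stands as a reason to keep the conditional rate as a description. It does not make that rate a comparison of randomised groups.

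**Imbalance would be visible elsewhere.** Completion, tolerance, anxiety preventing completion and compliance are all secondary outcomes, so a reader could see unequal shares beside the conditional rate. This is true and limits the harm, but seeing the imbalance does not correct the estimate.

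**The counts are chosen to reverse.** This is also true. The protocol gives no expected rates, and the direction of bias assumes that those lost from the denominator are less likely to eat the food.

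Two stronger readings are tempting, and the document does not support either.
- *That consumption is measured only after a negative result.* The paragraph after Box 2 plans the assessment in both arms without that limit. The outcome definition is narrower than the data collection.
- *That the time-to-challenge outcome also breaches intention-to-treat.* Its wording names an end point, not a population of completers. Non-completers have no observed value, and the only summary stated is that "Continuous variables will be summarised as medians with IQRs", but censoring is compatible with the text and is commonly left to an analysis plan, which is not shown. Starting the clock at referral is a legitimate measure of access. Waiting before randomisation adds noise to an arm comparison, not bias. At most this deserves a clarifying sentence.

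**Conclusion.** The point holds for the consumption outcome. The restriction to negative results is part of the outcome definition, so it is not a detail left to an unseen analysis plan, and a between-arm comparison on that definition is inconsistent with the article's own rule for all analyses.

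The size cannot be fixed from the document. Under the assumed counts, a difference of +9.8 points becomes -6.7. That rests on unequal shares of negative results (45/60 against 57/60) and on a home consumption rate inside the window above. It is the point estimate that changes sign; neither interval excludes zero.

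Severity is low. The outcome is exploratory in a pilot, and the primary safety and feasibility outcomes are unaffected.

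**What to change.** For any between-arm comparison, define the outcome as consumption of the challenged food at 1 month and at 6 months over all randomised participants, counting those without a negative challenge as not having reintroduced it. Because the instrument records a degree of consumption, state in advance which level on it counts as consuming the food. Keep the rate among participants with a negative challenge, labelled as descriptive and not as a randomised comparison.

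**Cost:** wording only. The assessment is already planned in both arms.

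**Downside:** the all-randomised figure mixes true allergy, non-completion and non-reintroduction after a tolerated challenge. Show both figures side by side, with the share of negative challenges in each arm, so that a reader can separate them.

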### Sample size and statistical analysis

A total of 120 participants (60 per arm) will be recruited for this pilot trial. This sample size will provide estimates of safety and recruitment feasibility outcomes with a precision of <20% (total width of CIs). The chosen sample size is also considered sufficient to generate reliable estimates of safety and potential efficacy for planning a future definitive trial, as precision gains diminish beyond approximately 60 participants per group for binary outcomes.^15^

All analyses will follow the intention-to-treat principle, with supplementary per-protocol analyses conducted for sensitivity. Continuous variables will be summarised as medians with IQRs, while categorical variables will be presented as frequencies and percentages.

Binary outcomes will be presented as counts and proportions with exact 95% CIs. Comparative analyses between study arms will report absolute risk differences and relative risks, each with 95% CIs, using generalised linear models with a binomial family and identity or log link functions as appropriate.

No interim analyses are planned for this pilot study. Missing data are expected to be minimal and, where necessary, will be described in reporting.

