### Eligibility criteria

Participants screened for the FoodCHOMP trial include all adults referred to outpatient allergy services with a reported food allergy label. Eligibility criteria were designed to maximise safety during food challenge procedures (Box 1). Inclusion criteria focus on individuals with negative SPT to the implicated food allergen at the time of screening and capacity to provide informed consent. Conversely, a range of exclusion criteria are applied to minimise risk, including the exclusion of specified medical conditions such as poorly controlled asthma, and use of medications that could interfere with challenge outcomes. These criteria are designed to identify a cohort considered low-risk for a severe allergic reaction and/or poor clinical outcome in the event of a severe allergic reaction (eg, uncontrolled asthma or advanced cardiac disease). Where participants have documentation of prior sensitisation to the selected food allergen (ie, previously positive skin tests or allergen specific IgE) skin testing was performed in duplicate. Patients with a reported food allergy label with a screen fail are eligible for the trial registry of the FoodCHOMP.

Box 1Inclusion and exclusion criteria
*Inclusion criteria*
Participants will be eligible for inclusion if they meet all of the following criteria:Aged 18 years or older.Referred to the outpatient allergy clinic with a reported food allergy label.Negative skin prick testing (weal <3 mm greater than the negative control) to the food implicated in their allergy label.Able and willing to provide informed consent.
*Exclusion criteria*
Participants will be excluded if any of the following criteria are present:Pregnancy.Poorly controlled asthma, defined as an Asthma Control Questionnaire-5 score >1 at the time of enrolment.History of food reactions inconsistent with IgE-mediated processes (eg, exclusively gastrointestinal symptoms, food protein-induced enterocolitis syndrome).Clear history of food-dependent exercise-induced anaphylaxis.Current use of medications that may influence the outcome of the challenge, including:Antihistamine therapy.Systemic corticosteroids at doses exceeding stress-dose thresholds (ie, >50 mg hydrocortisone four times daily or equivalent).Omalizumab or alternate biologic therapy.Any other illness or condition that, in the investigator’s judgement, would substantially increase the risk associated with participation in the study.

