### Randomisation

Eligible participants will be randomised in a 1:1 ratio to either the intervention arm (home-based food challenge) or the control arm (standard in-clinic food challenge). Randomisation will be performed using a permuted block design, stratified by hospital site, participant gender and evidence of prior sensitisation to the challenge food, to ensure balanced allocation across study arms.

The randomisation sequence will be generated in Stata and delivered through REDCap (Research Electronic Data Capture), hosted on secure servers at Austin Health. Allocation concealment will be ensured until the point of randomisation. Investigators and participants will not be blinded to group assignment due to the nature of the intervention.

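### If an arm has no immune-mediated events, the planned binomial models give no finite relative risk and, with Wald limits, too narrow a risk difference

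*Protocol article*

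**What the plan says.** The primary outcome is safety, "measured by the proportion of participants who experience an immune-mediated AE during the food challenge" (Outcomes). The size is fixed: "A total of 120 participants (60 per arm) will be recruited for this pilot trial".

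The section on sample size and statistical analysis uses two interval methods. For single proportions: "Binary outcomes will be presented as counts and proportions with exact 95% CIs". For the comparison, it plans both a risk difference and a relative risk with 95% limits. The method is stated as "using generalised linear models with a binomial family and identity or log link functions as appropriate". No other between-arm method is named for the primary outcome. The closing qualifier most naturally governs the choice of link (identity for the risk difference, log for the relative risk), not a move away from these models. The article does not state the interval type (Wald, profile or score), the covariates, or what happens if an arm has no events.

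No expected rate for the primary outcome is given anywhere. The Introduction describes a low-risk label as one that a challenge would probably show to be false, and the trial uses a negative skin test to define that group. It also acknowledges reported reactions after a negative skin test.

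**The concern.** Both models work well when each arm has a reasonable number of events. Neither works at zero. The log of a zero risk does not exist, so the relative risk has no finite estimate. The identity-link model fits the empty arm exactly at zero and gives it a standard error of zero, so that arm adds nothing to the width of a Wald interval, although 0 of 60 is far from proof of zero risk.

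The cohort is selected so that most challenges should be uneventful, which makes an empty arm a realistic result. The between-arm estimate is meant to help plan a larger trial of non-inferiority (Study design). If the true risk is higher at home, a risk-difference interval that is too short at its upper end understates the excess that the data still allow, which is the figure such planning needs. If the method is chosen only after the counts are seen, there would also be a choice between materially different safety limits.

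**Working it through.** **Inputs.** From the article: 60 per arm, exact 95% intervals per arm, and risk difference (RD) and relative risk (RR) from binomial models. Assumed: the true risks, since none is stated; the Wald interval, as the usual software default; and Clopper-Pearson for the exact interval. All differences are home minus clinic, in percentage points.

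**1. The plan's own precision figure.** The article claims a total confidence interval width below 20%. The exact width at n = 60 is 19.5 points at 9/60 and 20.2 at 10/60. At n = 120 it is at most 18.5 for any proportion. The claim therefore reproduces for a per-arm safety rate up to 15% and for proportions on all 120. It concerns single proportions and says nothing about the comparison.

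**2. How likely is an empty arm?** For one arm, P(0 events) = (1 − p)^60 = q. With equal risks, P(at least one empty arm) = 2q − q². At 2%: q = 0.98^60 = 0.298, so 0.595 − 0.089 = 0.507.

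| Assumed risk, both arms | At least one arm empty | Both empty |
|---|---|---|
| 1% | 79% | 30% |
| 2% | 51% | 8.9% |
| 3% | 30% | 2.6% |
| 5% | 9% | 0.2% |
| 10% | 0.4% | below 0.1% |

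One low-risk arm is enough. At 3% home v 1% clinic the chance is 62%, and at 5% v 1% it is 57%.

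**3. What the models then return.** *Log link:* with an empty arm, log(p1/p2) is infinite or undefined. In fitted examples the log RR had a standard error of about 12,700 or more, so the interval is useless because it is too wide.

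*Identity link with Wald limits:* d ± 1.96 × √[p1(1 − p1)/60 + p2(1 − p2)/60]. At 1 v 0: 0.0167 ± 1.96 × √(0.0167 × 0.9833/60) = 0.0167 ± 0.0324, or −1.6 to 4.9 points. At 0 v 0 both variance terms vanish and the interval is [0, 0].

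*Newcombe:* upper limit = d + √[(u1 − p1)² + (p2 − l2)²], with l and u the Wilson limits of each arm. At 0 v 0, u1 = 3.84/(60 + 3.84) = 6.0%, so the limits are ±6.0. At 1 v 0, u1 = 8.9% and l2 = 0, so the upper limit is 8.9.

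| Events, home v clinic | Wald RD upper | Newcombe upper | Miettinen-Nurminen upper |
|---|---|---|---|
| 0 v 0 | 0.0 | 6.0 | 6.1 |
| 1 v 0 | 4.9 | 8.9 | 8.9 |
| 2 v 0 | 7.9 | 11.4 | 11.4 |
| 3 v 0 | 10.5 | 13.7 | 13.8 |
| 3 v 1 | 9.7 | 12.1 | 12.3 |
| 6 v 3 | 14.4 | 15.7 | 15.9 |

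The gap closes as events accumulate. With at least one event in each arm, the unadjusted models converged in every table fitted.

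**4. Coverage of the nominal 95% RD interval.** Sum the binomial probabilities of all 61 × 61 tables whose interval contains the true difference.

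| True risk, home v clinic | Wald | Newcombe | Wald interval wholly below the truth |
|---|---|---|---|
| 2% v 2% | 98.0% | 99.6% | 1.0% |
| 3% v 3% | 96.0% | 98.8% | 2.0% |
| 5% v 5% | 94.0% | 97.3% | 3.0% |
| 10% v 5% | 94.3% | 96.5% | 3.6% |
| 5% v 2% | 93.9% | 98.3% | 5.1% |
| 3% v 1% | 83.4% | 99.5% | 16.1% |

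At 3% v 1%, 8.8 of the 16.1 points come from the 0 v 0 table. The other 7.3 come from other tables. The largest contributor among these is 0 v 1, with probability 0.161 × 0.332 = 5.3% and a Wald interval of −4.9 to 1.6, which excludes the true +2.

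**The case against.** The strongest reply has four parts.

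*Rarity is not documented.* The limitation about rare events concerns severe ones, and the eligibility text speaks likewise of severe reactions: "These criteria are designed to identify a cohort considered low-risk for a severe allergic reaction". The primary outcome is any immune-mediated event, including urticaria or vomiting, within a window of up to 48 hours. Previously sensitised patients can enter, and home dosing lasts 5 days. This stands, and it makes the point conditional on few events. The Introduction's definition of a low-risk label still makes few events plausible.

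*Wald is not in the text.* This also stands. A profile-likelihood interval from the same model gives about ±3.2 points at 0 v 0 and an upper limit of 7.1 at 1 v 0. That is better than Wald but still narrower than the score limits, and it does not rescue the relative risk. Interval type is often left to an analysis plan. What the article does fix is the model family, and it is that choice which fails at zero.

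*The bad coverage is selective.* With equal risks, coverage is at or near nominal and misses are symmetric, so the error is not always in the unsafe direction. This stands, with one qualification: when the true difference is zero, the degenerate [0, 0] counts as covering it.

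*The exact per-arm intervals protect the reader.* Largely true. 0/60 would be shown with an upper limit of 6.0% and 1/60 with 8.9%.

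A reader might infer that the planned comparison is bound to be unusable or falsely reassuring, that both measures come out too narrow, or that the two interval methods contradict each other. The documents do not support this. No rate is given, only the risk difference is too narrow, and an arm's risk and a difference in risks are separate quantities. Nor can it be inferred that the randomisation factors ("stratified by hospital site, participant gender and evidence of prior sensitisation to the challenge food") are ignored, because the article does not say either way.

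**Conclusion.** The point holds conditionally and is moderate. If an arm has no primary events, the log-link relative risk has no finite estimate, and the identity-link risk difference with Wald limits is too narrow by about 3 to 6 points at the upper end (0 v 0 to 3 v 0 events). Under assumed equal risks of 1% to 3% an empty arm has a 79% to 30% chance; at 5% it is 9%. Real harm to coverage needs a home risk above a very low clinic risk: at 3% v 1% it is about 83%, with nearly all misses understating the excess. With equal risks, or about 5% or more in both arms, coverage was about 94% or better in the cases examined.

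This rests on assumed event rates and an assumed Wald interval. It is not graver because the exact per-arm limits remain valid and the pilot applies no margin or test.

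**What to change.** For the immune-mediated event comparison, pre-specify an unstratified risk difference with a Miettinen-Nurminen or Newcombe score 95% interval. Report the relative risk, with a score interval, only when both arms have at least one event, and otherwise state that it cannot be estimated. Keep the binomial models for common binary outcomes such as challenge completion and tolerance. Adjustment for the randomisation factors is not sought for this outcome, because a handful of events cannot support it.

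The change is one or two sentences, made before outcome data are seen, and needs only standard software. The price is a somewhat wider, conservative interval when events are few: Newcombe coverage was 99.5% at 3% v 1% and 97.3% at 5% v 5%.
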